## Abstract

**Background:**

Adverse drug events could often be prevented. One of their main causes is that patients rarely know how to detect them. Another cause is inadequate communication between patients and physicians. If patients were to be effectively trained in detecting and reporting adverse drug events, this should help to prevent their occurrence and subsequent complications. Our purpose is to present the protocol of the InPAct trial, which aims to evaluate an interactive program that encourages patients to report adverse drug events in primary care.

**Methods/design:**

We will conduct a cluster randomised controlled stepped wedge trial, with eight clusters of 10 general practitioners each. The physicians will suggest to all of their antihypertensive-treated patients that they take part in this study. The InPAct program will be implemented in the clusters in random order along five successive three-month periods. Two new clusters will be trained in implementing the program at each step. The program features: an interactive patient booklet including informative paragraphs, several care plans and adverse drug event report forms; and standardised training of physicians in how to present the booklet to the patient. The primary outcome will be the reporting of adverse drug events by patients to their physician within three months. We assume that the number of patients reporting at least one adverse drug event will increase from 3% before program implementation to 7.5% afterward (coefficient of variation = 0.5, α = 0.05, β = 0.2), which means that 1,200 patients must be included. The effect of the intervention on the main outcome will be quantified and tested using a mixed logistic model to integrate cluster and time effects.

**Discussion:**

Our choice of a stepped wedge design is particularly appropriate for evaluating the implementation of a patient safety program within the constraints of general practice. We describe the InPAct intervention, which is an original program that is intended to improve communication between patients and physicians. Indeed, none of the previously published intervention studies has combined a patient education program and a patient reporting system for adverse drug events with the aim of improving patient safety in primary care.

**Trial registration:**

This study is registered in ClinicalTrials.gov NCT01610817.

## Background

According to a recent report of the Canadian Patient Safety Institute, the management of adverse drug events (ADEs) in primary medical care is a public health priority [1]. The proportion of patients presenting an ADE within the first three months following an ambulatory drug prescription was estimated to reach 25% in Gandhi et al. [2]. Cardiovascular drugs have been found responsible for 20% to 30% of hospitalisations for ADEs; meanwhile, 20% to 40% of ADEs could be prevented [2,3]. A lack of information and communication between patients and health care professionals has been identified as an underlying factor favouring the occurrence of ADEs [4,5]. A significant proportion of ADEs and associated complications could be prevented if risk situations were detected earlier and if patients were better informed about participating in their own medical care and about reporting ADEs [6]. In the InPAct (Information for Participating Actively) study, we focused on the reporting of ADEs by patients. Because clear differences have been shown between reports emanating from patients and those emanating from health professionals, it is essential that patients be able to report ADEs in order to supplement the reporting of ADEs by health professionals [7,8]. It has been found that patients report ADEs four times less often than do health professionals [7,9]. Considerable variations have been observed from one country to another in terms of the proportion of total ADE reports submitted by patients as opposed to the proportion submitted by health professionals [10]. In France, according to data from the ANSM (French National Agency for the Safety of Medicines and Health Products), only 1% of official ADE reports are made by a patient. We decided to focus on ADE reports made by antihypertensive-treated patients in primary care for three reasons. First of all, hypertension is common, with two-thirds of people older than 65 affected by this condition in developed countries [11]. Also, drug prescriptions for this sector of the population are often composed of at least four different drugs, which increases the risk of ADEs [12-14]. Finally, the proportion of patients experiencing at least one ADE within the first three months following the prescription of an antihypertensive has been estimated at 12.6% [2].

The InPAct intervention is an interactive program. It consists of educating patients about taking a more active role in their own care, so that they are more likely to report antihypertensive-related ADEs to their general practitioner (GP). Another important goal of the InPAct program is to improve patient safety in primary care.

Our purpose is to present the methodology and expected results of the InPAct trial. The primary outcome aims to evaluate the effectiveness of the InPAct program in promoting patient reports of ADEs. The secondary outcomes include the measurement of the InPAct program’s effectiveness in limiting ADE risk situations and in reducing the occurrence and severity of ADEs. The other secondary outcomes are the evaluation of the health knowledge and the level of satisfaction of antihypertensive patients with respect to the medical care provided by their GP.

## Methods/design

### Study design

The design of the InPAct protocol is a cluster randomised controlled (CRCT) stepped wedge trial design, which is appropriate for assessing the impact of patient safety interventions [15]. This design involves the sequential rollout of an intervention in the clusters over several time periods. The order in which the clusters will receive the intervention is determined at random, and by the end of the study, all clusters will have received the intervention. Finally, each cluster will successively be situated in a control group and then in an intervention group.

In the InPAct protocol, eight clusters of several GPs were defined. Four steps, one unit (U) of two clusters per step, and five periods (from P1 to P5) of three-month duration were defined. In the first period, the InPAct program will not be implemented. The InPAct program will be rolled out sequentially to the four GP cluster units over the last four time periods (Figure 1). The order in which the clusters will take part in the program is determined at random, allowing the full implementation of the intervention by all participating GPs by the end of the trial [16,17].

**Figure 1 F1:**
[figure not shown]
**InPAct study design.** One unit of randomisation (U1, U2…) contains two clusters of general practitioners, who implement the InPAct program during the same period of time (P2 to P5). Non-gray cells represent control units. Gray cells represent units in which the InPAct program was implemented.

### Setting

The InPAct program will take place in general practitioners’ offices of several suburban cities in three French regions (Rhône–Alpes, Auvergne and Ile-de-France).

### Recruitment of general practitioners

Eight clusters were defined, with ten GP volunteers per cluster. The GPs were grouped in a cluster according to criteria of geographic proximity, practice in the same medical centre, or interaction among professionals.

### Recruitment of patient participants

GP investigators involved in the study are required to recommend participation in this study to each patient over 18 years old who is consulting to initiate, modify or renew an antihypertensive drug prescription. In order to be included, the patients must meet the inclusion criteria, understand the investigator’s language, and agree to answer a telephone survey at home. Only the patients included in the study after the entry of their GP into the intervention group will receive the interactive booklet. Each patient will be followed during three months, with the outcome criteria collected at the end of this period.

### InPAct program

The InPAct program consists of providing an interactive booklet to the patients as well as standardised training to the GPs regarding the presentation of the booklet to the patient. A pilot study involving a small sample of patients and GPs has already made it possible to test the feasibility and acceptability of InPAct program implementation. This pilot study has provided some arguments in favour of a beneficial effect of the intervention [18].

### 1. InPAct booklet description

Ten steps were necessary to develop the InPAct interactive booklet [18]. This work was performed by a collaborative group including patients, GPs and other health professionals involved in ambulatory care or who specialised in one of the medical domains of the study. The initial booklet was created using the Delphi consensus method [19]. In a following step, a qualitative study made it possible to improve booklet content and booklet presentation instructions for GPs. Several tests of text readability and booklet reviews by communications professionals were repeated during the booklet creation process. The booklet was printed on both sides of a thick, film-coated, glossy A4-size paper folded into thirds. The title and instructions for use are on the outside. Informative paragraphs on hypertension, cardiovascular risk factors, situations involving a risk of ADEs and a list of the most frequent antihypertensive-associated ADEs are inside. Several ADE report forms and several care plans that can be annotated by the patient are included in the form of memo pads placed within the booklet.

### 2. General practitioner training

GP investigators will receive booklets and will participate in a web seminar explaining the kind of oral information to provide when the booklet is given to the patient. As determined by the pilot study, physicians are encouraged to give the booklet to the patient and to first present the principal value of the booklet for the patient, that is, the reporting of ADEs for increased patient safety [18]. In order to increase physician-patient interaction and communication, physicians are encouraged to first ask several questions to evaluate patient knowledge of the benefits and risks of the antihypertensive drug prescription, and to then give some complementary information. GPs are asked to present the care plan to the patient and to explain the antihypertensive drug prescription. Also, GPs are incited to explain the lab tests planned for the patient follow-up and to present to the patient the open text box for patient questions in the care plan. Once the booklet has been presented to the patient in this manner, GPs must again remind the patient of the main value of the booklet and describe the content of the ADE report form. Our hypothesis is that the InPAct booklet should facilitate the interaction between GPs, who are primary healthcare professionals, and their patients, leading to improve ADE reporting by patients.

### Comparator

The care management of antihypertensive-treated patients carried out by GPs belonging to the control group (*i.e.*, prior to InPAct program implementation in their cluster) will be identical to the usual practice. All outcomes will be assessed three months after patient enrolment, partly by the GP and partly through a phone survey of the patient. All outcomes will be identically collected in both control and intervention groups (Figure 2).

**Figure 2 F2:**
[figure not shown]
Diagram of the management of patients included in the InPAct study in both groups.

### Outcome measurement

The primary outcome of the InPAct study is the reporting of ADEs by antihypertensive-treated patients to their GP during the three-month period following enrolment. Patient reporting was defined as all patient reports to the GP of a medical issue for which the patient suggested a drug to be the cause. The secondary outcomes are: ADE-associated medical complications presented by antihypertensive-treated patients (*e.g.*, orthostatic hypotension, falls, renal failure, hydroelectrolytic disorders, dehydration, confusion syndrome, heart rhythm disorder, or hospitalisation); ADEs presented by antihypertensive-treated patients (reported or not); situations presenting a risk of ADEs for antihypertensive-treated patients; modification of the prescription by the GP, following an ADE; a patient knowledge evaluation (on hypertension and corresponding care, on benefits, risks and management of risk associated with drug prescriptions); and an evaluation of patient satisfaction.

### Data collection

When a patient is recruited for the study, the GP will need to enter the patient’s clinical data and prescription into an electronic case report form (e-CRF) (Figure 2). After three months of patient follow-up, the GP will have to collect data on ADE occurrence, patient ADE reporting and prescription modifications, for entry into the e-CRF. Also after three months of patient follow-up, clinical research associates are to interview patients using a standardised phone questionnaire dealing with ADE occurrence, situations presenting a risk of ADEs, ADEs that occurred without being detected by GPs, and patient skills and satisfaction concerning their medical care. The associates will have to enter the corresponding data into the e-CRF and will have to provide a detailed explanation of all drug prescriptions made by the GP.

### Sample size

Sample size calculations were carried out using the method implemented by Hussey and Hughes [20]. In our study, the number of clusters was fixed at eight, and the number of time periods was fixed at five. The expected effect of the intervention is an absolute increase of 4.5% of the percentage of hypertensive patients who will report at least one ADE; *i.e.*, an increase from 3% in the group without intervention to 7.5% in the group with intervention. The clustering induces an increase in the variance of the outcome criterion, due to inter-cluster heterogeneity; this increase is quantified by the inter-cluster coefficient of variation. For a given number of patients per cluster, the power of the study was calculated for different coefficients of variation between 0.1 and 0.5, which corresponds to the range of values usually observed. The inclusion of 240 patients per time period (30 patients per cluster) leads to a power greater than 80% regardless of the coefficient of variation (Table 1). The type I error was fixed at 5% for a bilateral test. In the context of the InPAct study, for logistical reasons and to avoid the risks of inter-cluster contamination and clusters with no inclusion, it was preferable to limit the number of GP clusters. With a classic CRCT parallel group design, the number of patients to include would have to be at least 6,000 to maintain a statistical power of 80% with 12 clusters (under 12 clusters it is impossible to reach a statistical power of 80%, regardless of the number of patients), but with our choice of stepped wedge design, the patient number decreases to 1,200 for eight clusters with a statistical power of 80%.

**Table 1 T1:** Statistical power calculated from the coefficient of variation and number of patients per time period

**Cv**	**184 patients per time period**	**208 patients per time period**	**240 patients per time period**
0	0.80	0.85	0.89
0.1	0.80	0.84	0.89
0.2	0.78	0.83	0.87
0.3	0.76	**0**.**81**	0.85
0.4	0.74	0.78	0.83
0.5	0.72	0.76	**0**.**81**

The expected percentage of hypertensive patients reporting at least one ADE is determined as follows: the proportion of patients with ADEs within the first three months of antihypertensive treatment has been estimated at 12.6% in Gandhi et al*.*[2]; and the frequency of ADEs reported by patients has been estimated to be four times lower than that reported by health professionals and seven times lower than that reported by GPs [7,9]. Our hypothesis is that when four patients experience an ADE, only one reports it. We have therefore estimated that prior to the implementation of the InPAct program, 3% of antihypertensive-treated patients would report an ADE.

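### The stated power above 80% with 1,200 patients appears to use the 3% rate's variance in every cell; with the plan's own 7.5% in the intervention cells, power is about 0.7 at CV 0 and 0.52 to 0.64 at CV 0.5

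*Protocol article*

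**What the plan says.** The Sample size section fixes the inputs. On method: "Sample size calculations were carried out using the method implemented by Hussey and Hughes". On layout: "the number of clusters was fixed at eight, and the number of time periods was fixed at five". On effect: "an increase from 3% in the group without intervention to 7.5% in the group with intervention". On error: "The type I error was fixed at 5% for a bilateral test". The Study design section adds the roll-out: four steps, two clusters crossing over at each, and a first period with no intervention.

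From these inputs the article concludes that 240 patients per period "leads to a power greater than 80% regardless of the coefficient of variation", and that with a stepped wedge "the patient number decreases to 1,200 for eight clusters with a statistical power of 80" per cent. The abstract ties the size to the least favourable row of Table 1 ("coefficient of variation = 0.5, α = 0.05, β = 0.2"), "which means that 1,200 patients must be included". The Discussion repeats 1,200 patients at 80% power as an argument for the design.

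The article does not state the within-cell variance, or the rate to which the CV applies.

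**The concern.** Period 1 is all control and two clusters cross at each step, so 2 × (4 + 3 + 2 + 1) = 20 of the 40 cluster-periods are intervention cells. Under the planning hypothesis their rate is 7.5%, with binomial variance 0.075 × 0.925 = 0.0694. The control cells have 0.03 × 0.97 = 0.0291. The ratio is 2.4.

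If the smaller figure stands for all 40 cells, the hypothesis enters the effect size but not the noise, and power is overstated. Table 1 is the stated basis for 1,200 patients, so what is at stake is the planned type II error of 20% and the size of effect that this trial can be said to be able to detect.

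**Working it through.** **Inputs.** I = 8 clusters, T = 5 periods, difference 0.045, two-sided 5% (Sample size section); two clusters per step (Study design section). Patients per cluster-period m: 184/8 = 23, 208/8 = 26, 240/8 = 30. From the roll-out, the number of intervention cells is U = 20, the sum of squared column totals is W = 0 + 4 + 16 + 36 + 64 = 120, and the sum of squared row totals is V = 2 × (16 + 9 + 4 + 1) = 60.

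**Formula** (Hussey-Hughes; fixed period effects, random cluster intercept), with s² = σ²/m and τ the between-cluster SD:

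Var = I·s²·(s² + Tτ²) / [(IU − W)·s² + (U² + ITU − TW − IV)·τ²]

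Here IU − W = 160 − 120 = 40, and U² + ITU − TW − IV = 400 + 800 − 600 − 480 = 120. Power = Φ(0.045/√Var − 1.96).

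**Reproducing Table 1.** Take σ² = 0.0291 and τ = CV × 0.03, with m = 30, so s² = 0.00097.

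- CV 0: Var = 8s²/40 = 0.000194, SE 0.01393, ratio 3.231, power 0.898.
- CV 0.5 (τ² = 0.000225): Var = 8 × 0.00097 × 0.002095 / (0.0388 + 0.0270) = 0.000247, SE 0.01572, ratio 2.863, power 0.817.

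| CV | 0 | 0.1 | 0.2 | 0.3 | 0.4 | 0.5 |
|---|---|---|---|---|---|---|
| Computed, 240 per period | 0.898 | 0.893 | 0.879 | 0.859 | 0.837 | 0.817 |
| Table 1 | 0.89 | 0.89 | 0.87 | 0.85 | 0.83 | 0.81 |

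The other two columns match in the same way. All 18 entries equal the computed value cut off at two decimals. Keeping σ² = 0.0291 but scaling the CV to 5.25% or 7.5% breaks the match. With the mean-rate or 7.5% variance, no entry is matched.

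**Letting both rates into the variance.** The mean rate is (3% + 7.5%)/2 = 5.25%, so σ² = 0.0525 × 0.9475 = 0.0497 and s² = 0.001658 at m = 30.

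- CV 0: Var = 0.000332, SE 0.01821, ratio 2.471, power 0.695.
- CV 0.5, τ = 0.5 × 0.03 = 0.015: Var = 0.000396, SE 0.01989, ratio 2.263, power 0.619.
- CV 0.5, τ = 0.5 × 0.0525 = 0.02625: Var = 0.000454, SE 0.02131, ratio 2.111, power 0.560.

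Other defensible variances, still with 30 per cell and period effects:

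| Within-cell variance | Rate to which the CV applies | CV 0 | CV 0.5 |
|---|---|---|---|
| Mean rate, 0.0497 | 3% | 0.695 | 0.619 |
| Mean of the two variances, 0.0492 | 3% | 0.700 | 0.623 |
| Cell-specific (generalised least squares) | 3% | 0.711 | 0.636 |
| Mean rate | 5.25% | 0.695 | 0.560 |
| Mean of the two variances | 5.25% | 0.700 | 0.564 |
| Cell-specific | 5.25% | 0.711 | 0.584 |
| Cell-specific | each cell's own rate | 0.711 | 0.522 |

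**Cross-checks on the logistic scale.** A logit approximation gives 0.678 at CV 0 and 0.562 at CV 0.5. Two simulations of a mixed logistic model with period effects (1,500 and 2,500 runs, Wald test) gave 0.683 and 0.648 at CV 0, and 0.604 and 0.587 at CV 0.5. The shortfall does not come from the linear approximation.

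**Detectable rate.** Solving for the intervention rate that gives 80% power against 3% with 30 per cell yields 8.1% (cell-specific) to 8.3% (mean rate) at CV 0. At CV 0.5 it is 8.7% to 10.6% over the conventions in the table.

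**The case against.** The strongest objection is that the article never states its variance, so the use of the 3% figure is an inference. That stands, and the point should be worded accordingly. The inference is nonetheless strong, because one simple choice reproduces 18 entries and the alternatives tried fail.

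It can also be said that the formula takes a single common variance. It does, but a common variance has to represent both kinds of cell, and here they are split evenly. Appeal to the variance under the null does not help either: the planned model takes its standard error from data in which, under the alternative, half the cells run at 7.5%.

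Leaving out period effects would raise power to between 0.92 and 0.94 (cell-specific variances). That does not match Table 1 or the analysis with time effects announced in the abstract.

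A reader might infer that the true power is 56 to 70%. The document does not support so definite a figure. That range belongs to one variant, which also rescales the between-cluster SD to the 5.25% mean rate. Correcting the binomial variance alone leaves 0.62 to 0.64 at CV 0.5, whereas scaling the SD with the cell rate gives 0.52. The article does not say which convention applies.

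A reader might also infer that a null result will be taken as evidence against the program. Nothing in the article says so. Nor does lower power by itself bias the estimate or inflate the type I error.

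**Conclusion.** The claim of more than 80% power at every CV with 1,200 patients does not hold under the article's own rates. Every variant run that lets the 7.5% rate into the variance and keeps period effects stays below 80% for CV 0 to 0.5. It fails even at CV 0, where the scaling of the CV plays no part.

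Power is about 0.70 to 0.71 at CV 0, against 0.89 stated. At CV 0.5, the value on which the abstract rests the sample size, the stated figure is 0.81. The recomputed figure is 0.62 to 0.64 if the CV applies to 3%, 0.56 to 0.58 if it applies to 5.25%, and 0.52 if it applies to each cell's rate. The type II error at the planned effect is thus about 0.3 at CV 0 and 0.36 to 0.48 at CV 0.5, not 0.2.

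This assumes 30 patients in every cluster-period, the roll-out as described, and no losses. The cause, the 3% variance used throughout, is inferred from the match. The shortfall itself follows from the stated rates and layout, whatever its cause.

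**What to change.** Recompute Table 1 with a within-cell variance that reflects both rates, either mean-rate or cell-specific. State that variance and the rate to which the CV applies. Restate the power for 1,200 patients in the abstract, the Sample size section and the Discussion: about 0.7 at CV 0, falling to a value between 0.52 and 0.64 at CV 0.5 according to the convention chosen.

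Under the same convention, report the intervention rate detectable with 80% power against 3%: roughly 8.1 to 8.3% at CV 0, and a value between 8.7 and 10.6% at CV 0.5.

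The change is to text and one table. It requires no extra patients and leaves design and analysis as they are. The Trial status section says that enrolment has begun but data cleaning and analysis had not at submission, so as of then the restatement could still precede any analysis. The cost is a less favourable stated power.
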